## Methods

### Subjects and Design

The study will be conducted as a randomized controlled trial, performed at the EILO clinic at Haukeland University Hospital in Bergen, Norway, a nationwide referral center, annually seeing ~200 new patients. All study participants will be recruited from this EILO clinic. The design is outlined in Figure 2. After the diagnostic CLE test, all eligible patients will receive written information about the study. A nurse, not otherwise involved in the study, will provide oral information and be available for questions. Consenting participants will sign a written consent form before inclusion. For patients under the age of 16, their parents must also sign the form. Patients who decline participation will be offered treatment according to present department strategy; i.e., based on a “best practice” approach and according to current department policy for follow-up. We will need 140 patients in phase 1 and 30 patients in phase 3 (see statistics). However, our clinical experience is that ~10% of EILO patients are referred for surgery. The total number of included patients will then be 350.

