## The Study Phases

**Phase 1:** This is the main treatment period.

Consenting patients, irrespective of EILO subtype, will randomly be allocated into one of four treatment arms:

A. Basic information and breathing advice with biofeedback (IBA). This is the reference treatment against which the other methods will be measured.B. IBA plus inspiratory muscle training (IMT).C. IBA plus speech therapy.D. IBA plus both inspiratory muscle training and speech therapy.

**Phase 2:** Patients from group A (the reference group) who still fulfill the inclusion criteria will be offered treatment corresponding to group D; i.e., both IMT and speech therapy. For the other groups, Phase 2 will consist of waiting, testing the long-term effects of any effects gained from the interventions performed in Phase 1. Participants with no further complaints and who do not fulfill the criteria for surgery will stop follow-up after Phase 2.

**Phase 3:** Patients whose *supraglottic* CLE score still ≥2 and who otherwise fulfill the criteria for surgical intervention despite non-invasive treatment, will be offered to be randomized to (E) supraglottoplasty—full procedure or (F) supraglottoplasty minimally invasive procedure or (G) no surgery; the latter serving as the reference group for (E) and (F).

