### Power Analysis

For practical reasons, we perform the power analysis for a simpler model, where the baseline score is not included. The distribution of CLE scores 2–6 for patients referred to our clinic and meeting the inclusion criteria has been searched in our EILO registry, and found to be 23, 45, 25, 5, and 2%, respectively. We expect that the control group will have a similar distribution, and use this as the basis for the power analysis. We postulate that one of the factors will be effective, with an odds ratio (OR) of 0.3, the other factor will have zero effect (OR = 0) and that there is no interaction. This corresponds to a reduction in mean CLE score of 0.53 for the effective treatment, from 3.18 to 2.65, and is both clinically relevant and in line with effect sizes observed in previous studies (10). The distribution of CLE scores 2–6 will then be 50, 38, 10, 2, and 1%, respectively. (We expect that in practice, some of the patients will have scores below 2, so 2 on this scale should be interpreted as ≤2.) With 35 patients in each arm, computer simulations show that this will give a power of 90% for an overall test of difference between the four arms (even when not using the rule about removing insignificant interactions). An alternative model, where the two treatments have the same effect (OR = 0.3) but there is no additional effect of having both treatments (i.e., a negative interaction) gives a power of 80%. In the actual study, we expect that the baseline score will be a good predictor of the outcome, which will further increase the power.

For the surgical part of the study, the power analysis is similar, with the “no surgery” arm having the same distribution of CLE scores as before (mean score 3.18). However, the effect of the two procedures is postulated as being much larger, OR = 0.05, which corresponds to a mean score in both surgery arms of 2.17. This difference in mean scores of 1.01 is in line with effect sizes from a previous study (11). Including 14 patients in each of the three groups will give a power of ~98% for an overall test (before any adjustment for the baseline scores), and 89% for pairwise comparisons (adjusted for multiple comparisons). The back-up chi-squared test will have a power of 90%. By clinical experience, surgical treatment is provided to ~14% of our EILO population, thus 42 patients entering Phase 3 is a reasonable estimate.

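### The sample-size figures for Phase 1, Phase 3 and the total do not agree, and the only Phase 1 power given is for 140 patients although about 300 to 350 appear to be randomised

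*Protocol article*

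**What the plan says.** Subjects and Design sets the targets: "We will need 140 patients in phase 1 and 30 patients in phase 3 (see statistics"). It adds that "our clinical experience is that ~10% of EILO patients are referred for surgery", and concludes: "The total number of included patients will then be 350".

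The Study Phases describes entry to Phase 1: "Consenting patients, irrespective of EILO subtype, will randomly be allocated into one of four treatment arms". Phase 3 is for patients who still qualify for surgery after the non-invasive treatment. Phase 3—Surgical Intervention adds that this non-invasive algorithm is stricter than in routine care.

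Power Analysis gives Phase 1 power at one size only. For one effective factor with an odds ratio of 0.3: "With 35 patients in each arm, computer simulations show that this will give a power of 90" per cent. For the alternative in which both treatments work but do not add up: "there is no additional effect of having both treatments (i.e., a negative interaction) gives a power of 80" per cent. The ineffective factor in the main scenario is described thus: "the other factor will have zero effect (OR = 0"). For Phase 3 the section uses 14 patients in each of three groups and says that "surgical treatment is provided to ~14% of our EILO population, thus 42 patients entering Phase 3 is a reasonable estimate".

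Design and Randomization bases the main analysis on patients with complete follow-up and replaces losses arm by arm. It gives neither a cap at 140 nor a date for the Phase 1 analysis.

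**The concern.** Two things do not fit together.

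First, the total of 350 exists to feed Phase 3, but Phase 3 has two different sizes (30 and 42) and two different surgery rates (about 10% and about 14%). A reader cannot rebuild 350 from either pair.

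Second, if Phase 3 is filled from patients who have been through Phase 1, the number randomised in Phase 1 is the total and not 140. The stated Phase 1 power then describes a smaller trial than the one planned. The 35-per-arm target and the replacement rule point to a fixed 140. The complete-follow-up rule with no cap points to everyone.

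The choice affects the result. The standard error of a treatment effect shrinks roughly with the square root of the sample size. In addition, the interaction term is dropped when its P value is 0.20 or more, so the analysis size influences which model is reported. If the choice stays open until Phase 1 data exist, it could be made with results in view.

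**Working it through.** **Inputs, all from the article unless marked.**
- Phase 1: 140 patients, 35 in each of four arms, equal allocation.
- Phase 3: 30 patients at about 10% (Subjects and Design), or 42 at about 14% (Power Analysis).
- Total: 350.
- Control distribution of scores 2 to 6: 23, 45, 25, 5 and 2%. Effective odds ratio: 0.3.
- Assumption: 5% significance level for the overall test. The article states 0.05 only for the baseline-score term.

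**1. Can 350 be derived?** Total needed = Phase 3 patients / surgery rate.
- 30 / 0.10 = 300
- 42 / 0.14 = 300
- 42 / 0.10 = 420
- Backwards: 350 × 0.10 = 35 and 350 × 0.14 = 49, neither of which is a stated Phase 3 size.
- 350 would follow from 35 / 0.10 or 42 / 0.12, but neither 35 surgical patients nor a 12% rate appears.
- With 140 patients only, Phase 3 would receive 140 × 0.10 = 14 to 140 × 0.14 ≈ 20. This is why a larger total is needed.

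**2. How many are randomised in Phase 1?** Inclusion follows consent, consenting patients are allocated to the four arms, and Phase 3 takes those who still qualify after non-invasive treatment. No other entry to Phase 3 is described. The Phase 1 number is therefore about 300 (75 per arm) to 350 (about 87 per arm).

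**3. Reproduce the stated power at 35 per arm.** Multiplying the odds of a higher score by 0.3 gives 50, 38, 10, 2 and 1% and moves the mean from 3.18 to 2.65, as the article says. The overall four-arm test (3 degrees of freedom, no baseline score) was simulated with a proportional-odds likelihood-ratio test and cross-checked with a Kruskal-Wallis test:

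| Per arm | Scenario | Likelihood ratio | Kruskal-Wallis | Stated |
|---|---|---|---|---|
| 35 | one effective factor | 89.5% | 89.7% | 90% |
| 35 | negative interaction | 79.4% | 78.6% | 80% |
| 75 | one effective factor | not run | 99.9% | none |
| 75 | negative interaction | not run | 98.8% | none |
| 87 | one effective factor | about 100% | about 100% | none |
| 87 | negative interaction | 99.3% | 99.6% | none |

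The stated figures reproduce at 35 per arm. At 75 to 87 per arm, power is about 99 to 100% in both scenarios.

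**4. What the choice of analysis set is worth.** The standard error with 140 patients, relative to all patients, is √(300/140) = 1.46 to √(350/140) = 1.58 times as large.

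**5. The odds ratio of 0.** No effect is an odds ratio of 1; zero is its logarithm. The reproduction in step 3 uses 1. With a literal 0, every patient given that factor falls in the lowest category, and simulated power at 35 per arm is 100%, not 90%.

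**6. Phase 3.** At 14 per arm the overall power is 98.3% (stated about 98%). At 10 per arm, the 30 patients in Subjects and Design, it is 92.5%. The stated Phase 3 power therefore belongs to 42 patients and not to 30.

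**The case against.** The strongest reply is that 140 and 350 do different jobs. The first is what Phase 1 needs and the second is what Phase 3 needs, and the article says why the total is larger. The Phase 1 power is right for 140, and a surplus only raises it. Nobody is misled about the risk of missing an effect. This stands, and it limits the point to inconsistent and incompletely fixed figures.

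It can also be said that the time of analysis belongs in a fuller document, and that the flow chart, which is not shown here, may settle who enters Phase 1. The first part is fair as far as timing goes. It does not explain two Phase 3 sizes, two surgery rates and a total that matches neither. The second part is a real limit: that everyone passes through Phase 1 is inferred from several sections and not stated in one sentence.

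A reader might go further and infer that the plan throws away 350 − 140 = 210 randomised patients, or that it tests at 140 and again at 350 and so inflates the type I error. The article supports neither. It sets no cap at 140 and describes no second test. Its rule of analysing patients with complete follow-up, read literally, is closer to one analysis of everyone. Both outcomes are only risks of leaving the analysis set unfixed.

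The odds ratio of 0 is a slip whose meaning is clear from the words beside it. It adds no weight to the main point.

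**Conclusion.** The point holds as an inconsistency in stated figures. Phase 3 is 30 patients at about 10% in one section and 42 at about 14% in another. Both imply a total of 300, the mixed pair of 42 at 10% implies 420, and none gives 350. The only Phase 1 power reported, 90% and 80%, is correct for 140 patients. It is not the power for the roughly 300 to 350 who appear to be randomised, which is about 99 to 100%. The error is in the conservative direction. The practical gap is that a reader cannot tell whether the primary comparison rests on 140 patients or on all of them.

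This rests on three assumptions: a 5% overall test, the article's own control distribution and odds ratio of 0.3, and Phase 3 being supplied only from Phase 1. The last is the natural reading but is inferred.

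**What to change.** 1. Choose one Phase 3 size and one surgery rate, derive the total from them with the division shown, and use the same three numbers in Subjects and Design and in Power Analysis.
2. State that the Phase 1 primary analysis is done once, on all patients randomised in Phase 1, and restate the power at that number. If an earlier result is wanted, name the first 140 as the only confirmatory set before any results are seen, and call analyses of later patients descriptive.
3. Say explicitly whether every Phase 3 patient must first be randomised in Phase 1.
4. Correct the odds ratio of the ineffective factor from 0 to 1.

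The changes are wording plus a rerun of the existing simulation, and they add no patients to the planned intake. The cost of analysing everyone is time. The clinic sees about 200 new patients a year, so 210 patients beyond the first 140 would take at least 210/200 ≈ 1.05 years even if every new patient took part. With a reconciled total of 300, the extra 160 would take at least 160/200 = 0.8 years.

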**Figure 2 F2:**
[figure not shown]
Flow chart depicting the four non-invasive approaches and two different surgical approaches. During Phase 1, breathing advice will be provided to all groups, and constitutes the only measure in group A, serving as reference for the groups B, C, and D.

The regional ethical committee of Western Norway approved the study (REK 2020-134444), and the study is registered in Clinical trials 2020/134444.

### Inclusion Criteria

EILO with CLE score at peak exercise graded as ≥2 at glottic *or* supraglottic level **and**Respiratory complaints to an extent that the patient feels a need for further treatment and follow-up.

### Exclusion Criteria

Breathing problems other than EILO, except well-controlled asthma.Perceived to be unable to perform repeated maximal cardiopulmonary treadmill exercise tests, or failing to accept the procedures required for repeated successful CLE tests, or unable to perform any of the other examinations required by the protocol.Abnormal anatomy at rest in the laryngeal region or the upper airways.Age below 12 years.

## The Study Phases

**Phase 1:** This is the main treatment period.

Consenting patients, irrespective of EILO subtype, will randomly be allocated into one of four treatment arms:

A. Basic information and breathing advice with biofeedback (IBA). This is the reference treatment against which the other methods will be measured.B. IBA plus inspiratory muscle training (IMT).C. IBA plus speech therapy.D. IBA plus both inspiratory muscle training and speech therapy.

**Phase 2:** Patients from group A (the reference group) who still fulfill the inclusion criteria will be offered treatment corresponding to group D; i.e., both IMT and speech therapy. For the other groups, Phase 2 will consist of waiting, testing the long-term effects of any effects gained from the interventions performed in Phase 1. Participants with no further complaints and who do not fulfill the criteria for surgery will stop follow-up after Phase 2.

**Phase 3:** Patients whose *supraglottic* CLE score still ≥2 and who otherwise fulfill the criteria for surgical intervention despite non-invasive treatment, will be offered to be randomized to (E) supraglottoplasty—full procedure or (F) supraglottoplasty minimally invasive procedure or (G) no surgery; the latter serving as the reference group for (E) and (F).

### Questionnaires

All patients will complete custom-made questionnaires recording demographic background variables and symptom scores; for details. The questionnaires focus mainly on respiratory symptoms experienced by the patients, treatment they have been exposed to, and diagnoses they have been assigned. Relevant co-morbidities will also be recorded.

## Detailed Descriptions Of The Applied Test Set-Ups

### Pulmonary Function and Exercise Test

Spirometry will be performed with Vyntus and MasterScreen on SentrySuite software (Vyaire Medical, Hoechberg, Germany) according to guidelines (29). The following expiratory and inspiratory volumes and flows will be recorded: Forced expiratory and inspiratory volume capacity (FVC and FIVC), forced expiratory and inspiratory volume in first second (FEV1 and FIV1), forced expiratory and inspiratory flow at 50% of FVC (FEF and FIF50) and at 25–75% of FVC (FEF and FIF25-75). Whenever possible, raw data will be standardized for age, height, and sex and presented as z-scores and percent predicted (30). The inspiratory and expiratory configuration of the flow-volume loops will be recorded and classified. Prior to testing, the equipment will be calibrated according to the manufacturer's guidelines.

### Continuous Laryngoscopy Exercise Test (CLE-Test)

A diagnostic CLE test will be performed as part of the standard workup for all patients received at the EILO clinic. All study participants will run to symptom-limiting distress or exhaustion on a treadmill (Woodway ELG 70, Weil am Rhein, Germany), wearing a head-set and face mask (Hans Rudolph, Inc., Kansas City, MO, USA) to secure a transnasal fiberoptic flexible laryngoscope (Olympus, Tokyo, Japan) in the best possible epipharyngeal position, ensuring a good view of the larynx. The patient is connected to a Vyntus cardiopulmonary exercise (CPX) unit (Vyaire Medical) and a 12-lead ECG (Marquette Medical Systems Inc., Milwaukee, WI, USA). An integrated set-up combines the data from the CPX unit and the laryngoscope, as well as a soundtrack and a video recording of the upper part of the body. The treadmill will be run according to a computerized protocol, incrementing speed, and/or grade every 1 min, aiming to obtain peak oxygen uptake after 6–12 min of exercise. All information will be stored in a computer file for later assessment. The test will be considered successful if the patient reproduces his or her respiratory complaints, or indicate exhaustion, preferably supported by a plateau in oxygen consumption and/or heart rate, and respiratory exchange ratio (RER) exceeding 1.10.

#### The CLE Scoring Procedure

Two highly experienced raters will score all CLE tests according to a system that has been published previously (18). EILO will be graded based on the severity of the visual obstruction of the supraglottic and glottic structures during exercise, with scores from 0 (complete patency) to 3 (almost complete closure) at the glottic and supraglottic level at moderate and at maximum intensity (Figure 3) (2, 18, 19). Both raters have assessed CLE recordings from ~3,000 individuals (18). The raters will review the video recordings retrospectively and not in the test situation, with recordings presented to each rater blinded to the identity of the patient and to whether the recordings were obtained before or after the intervention. Cases where scores differ between the two raters will be solved by consensus.

**Figure 3 F3:**
[figure not shown]
CLE grading system, reproduced with permission from Fretheim Kelly et al., Frontiers in Physiology (31).

#### Measuring Translaryngeal Resistance

Patients eligible for surgical intervention (Figure 2) will perform CLE tests that include also measurements of translaryngeal resistance, thus providing outcome measures not subject to any form of bias by the raters. The method has been described in a previous communication (21). Briefly, calculation of resistance is based on pressure recordings obtained from two pressure sensors placed above and below the larynx, and the airflow measured at the mouth. The vocal fold and proximal trachea will be anesthetized by lidocaine administered *via* an Olympus Spray tip catheter PW-6C-1 producing a lidocaine mist. Two pressure sensors (Mikro-Cath 825-0101, Milar, Houston, USA) will be introduced through a work channel in the laryngoscope, the first positioned approximately corresponding to the fifth tracheal ring and the second at the tip of the epiglottis. Both sensors are connected to a data acquisition box (Powerbox 8/35, AdiInstruments, Oxford, UK), collecting the data at 40 Hz, stored on a MacBook laptop using LabChart 8.0 software. Maximum inspiratory translaryngeal resistance will be determined at exhaustion; i.e., using ~10 breaths during the last 10 s of the CLE test, using this equation: [RL = PT – PE/AF] where RL is Laryngeal resistance (cm H_2_O/Ls-1), PT is Tracheal pressure reading (cm H_2_O), PE is Epiglottic pressure reading (cm H_2_O), AF is Airflow in Liters per second.

## The Treatment Interventions

### Information and Breathing Advice With Bio-Feedback (IBA)

Information and breathing advice (IBA) involving also an element of biofeedback will be provided to all groups. IBA has been provided in a relatively similar way to all patients diagnosed with EILO at our clinic during the past ~10 years, irrespective of provision of any other forms of treatment. This will not be altered in this study. Thus, a standardized version of our “IBA with biofeedback” treatment will serve as an “active comparator” treatment arm. The maximum time allowed for IBA and biofeedback in this study will be 30 min. The teaching will be provided by the attending physician and the test leader together. There will be a checklist for each patient, ensuring that all elements are covered, and provided similarly to all patients.

#### Before Starting the CLE-Test

After the laryngoscope has been secured in the correct position (see above, CLE-test), the patient will be shown his/her larynx on the monitor. The test leader points out important anatomical structures and landmarks, like the base of the tongue, the epiglottis, the cuneiform tubercle, the aryepiglottic fold, the true and false vocal cords and the tracheal inlet. The patient will then be asked to perform various breathing manoeuvers while observing his/her larynx. First: Breathe normally, then deep and rapidly—in order to assess supraglottic movements at rest. Next: Sustained vowel “e,” both a long “eeeee” and several short “e”s—in order to evaluate laryngeal symmetry and motion. Thereafter: Alternate between voluntary making “stridor-like noise” vs. not making “stridor-like noise” during inspiration.

The objective of this part of the protocol is to examine the laryngeal function at rest and to provide the patient with some basic knowledge on laryngeal anatomy and function in a quiet atmosphere.

The CLE test then starts, and will be performed as described above.

#### After the CLE Test

1) Immediately after finishing the CLE test, the mouthpiece will be removed, but the laryngoscope will be kept in place. The patient will then be asked to turn to face the monitor showing the laryngoscopy recording. While still having ongoing symptoms, important structures and landmarks will be pointed out, and the paradoxical movements will be thoroughly described to the patient.2) Patients in need of guidance to make symptoms abate and patients who panic will carefully be guided through the techniques described below under item 4, in order to obtain control of their laryngeal obstruction.3) When symptoms have stopped and the patient is able to receive information, there will be given a series of standardized teaching lessons. These lessons will be provided to the patients while the laryngoscope is left in place, in order to allow the patients to observe their larynx on the monitor while performing the exercises listed below.a. Reproduction of symptoms: The patients will be asked to repeat what he/she did before the CLE test started; i.e., alternate between intentionally making “stridor-like noise” vs. making no “stridor-like noise” during inspiration while watching the laryngeal movements on the monitor. The goal of this session is to make the patients understand what takes place in their larynx when they make “stridor-like noise” during inspiration. The session will go on for as long as it takes to grasp this information.b. Posture: The patients will be explained and shown that keeping the head high and lifted, and the shoulders low and retracted, are the preferred posture to ensure optimal and unobstructed breathing.c. Breathing muscles:i. It will be explained and shown how the patients should relax their shoulder girdle and perform diaphragmatic breathing rather than clavicular breathing.ii. The patients will be asked to breathe by expanding the thorax and the rib cage and to inhale quietly and deeply, attempting to avoid using the muscles around the throat or neck for assistance, while actively being coached to relax the muscles in the shoulder girdle. If necessary, the test leader will put the palm of his/her hand on the patient's chest or on both sides of the lower ribcage and ask the patient to inhale while lifting the arms and the hands.iii. Thereafter, the patient will practice the above (item i and ii), producing 5–10 rapid breaths, ensuring that the thorax moves as explained.iv. It will be explained and shown that focusing on exhalation rather than on inhalation may also help to redirect focus from clavicular obstructed breathing to diaphragmatic unobstructed breathing.4) Learning techniques to prevent or stop future EILO episodes.a. First of all, the patients will be explained the importance of keeping calm, avoiding increasing the respiratory rate, suppressing the urge to hyperventilate and—importantly—**not panicking**. The patients need to understand that an EILO attack is not deadly or dangerous.b. The patients will be explained and shown that forced inspiration might lead to more laryngeal obstruction, and that **focusing on exhalation** might help.c. The patients will learn different **breathing techniques** they can use to avoid laryngeal obstruction in situations where they sense that EILO is about to occur:i. Sniffing/inhaling through the nose or through closed teeth (Karlsen's maneuver).ii. Put the tongue behind the incisors during inhalation.iii. Try to yawn and breathe in and out during the yawn.5) In patients where panicking is part of the problem, the patients will learn that a good posture will help, together with lifting their arms over the head and down again. This maneuver implies lifting the rib cage, thus aiding the inspiration.

The aim is to help the patients to develop a strategy on how to control his/her larynx during exercise, and to be able to continue exercising without experiencing dramatic EILO incidents. The patients will be informed that the best approach is to start practicing while performing low to moderate intensity exercise, and then gradually increase the intensity as they become more confident. It will be emphasized that the new breathing technique they are about to adopt will need to be repeated until it becomes adopted as a part of their automated breathing pattern.

For all three non-invasive treatment groups, there will be a video meeting 1 and 3 weeks after the in-house training session, lasting a maximum of 30 min. The patients will be asked to demonstrate how they perform their breathing practices, and corrected when necessary.

